**Methods/Design:**

The sample will be composed of 24 children with CP between four and 12 years of age. After the signing of the statement of informed consent, the children will be randomly allocated to two groups: a control group using AFOs alone and an experimental group using both posture-control insoles and AFOs. Evaluations will be performed on five occasions: without any accessory (insoles or AFOs), immediately after, one month after, six months after and one year after AFOs or insole and AFOs use. The evaluation will involve the analysis of gait, static and functional balance, mobility and hypertonia. The three-dimensional assessment of gait will involve the eight-camera SMART-D SMART-D 140® system (BTS Engineering), two Kistler force plates (model 9286BA) and an eight-channel, wireless FREEEMG® electromyography (BTS Engineering). Static balance will be assessed using a Kistler force plate (model 9286BA). Clinical functional balance and mobility will be assessed using the Berg Balance Scale, Timed Up-and-Go Test and Six-Minute Walk Test. The posture-control insoles will be made of ethylene vinyl acetate, with thermal molding for fixation. The fixed orthoses will be made of polypropylene and attached to the ankle region (AFO). The results will be analyzed statistically, with the level significance set to 5% (p < 0.05).

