### Instruments

The Gross Motor Function Classification System for Cerebral Palsy (GMFCS) will be used to classify the children based on the level of gross motor function [17]. This system classifies children between Levels I and V. Only children classified at Levels I and II will participate in the proposed study.

The motor growth curves [18] referring to GMFCS Levels I, II and III will be used as a complement to the classification of gross motor function. The curves have the scoring of the GMFM-66 [19,20] on the vertical axis and age on the horizontal axis for each GMFCS level. Using these curves, the child is functionally classified as being within the expected range, better than expected or poorer than expected.

The Berg Balance Scale will be used for the assessment of functional balance. This scale consists of 14 tasks that are similar to different activities of daily living. The items are scored on a five-point scale ranging from 0 (inability to perform task) to 4 (ability to perform task independently). The maximal score is 56 points. The point system is based on the time in which a position is maintained, the distance to which the upper limb is capable of reaching out in front of the body and the time needed to complete a task. The execution time is approximately 20 minutes. A chronometer, stool and chair are needed for the assessment. The evaluation is performed with the child dressed and making use of his/her habitual orthosis and/or gait assistance device [21,22].

The Timed Up-and-Go Test will be performed and distance will be measured using a metric tape. This fast, practical, easy-to-apply test is widely used for the assessment of functional mobility and dynamic balance. The test quantifies functional mobility through the time (in seconds) in which an individual performs the task (stand up from a standardized chair with back and arm supports, walk three meters, turn around, walk back to the chair and sit down again) [23,24].

The Six-Minute Walk Test will be performed. This test is a reliable measure for the assessment of physical fitness [25,26] and quantifies (in meters) functional mobility through the distance traveled walking in six minutes. This test will be performed based on the guidelines of the American Thoracic Society.

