### Procedures

The children selected (whose legal guardians agreed to their participation by signing a statement of informed consent) will be evaluated regarding their anthropometric data and GMFCS classification and randomly allocated to the experimental and control groups. The control group will make daily and constant use of the AFOs. The experimental group will make use of the posture-control insoles for six hours daily during the most active period of the day and will remain using the AFOs the rest of the day.

The evaluation process (before, immediately after, one month after, six months after and one year after insole use) will be performed under two different conditions. Under the first condition (evaluation 1), the children will not use an assistance device and under the second condition (evaluation 2), the children will use either the posture-control insoles or the AFOs, depending on the group to which they belong. Evaluation 1 and evaluation 2 will be performed by different examiners. Examiner 1 will not be aware of which group the children belong, thereby characterizing the investigation as a blind study.

The evaluations will be held on two non-consecutive days. The Berg Balance Scale, Timed Up-and-Go Test, Six-Minute Walk Test and modified Ashworth scale will be administered on the first day. The three-dimensional gait analysis and the static balance test on a pressure plate will be performed on the second day.

For the three-dimensional gait analysis, the equipment will be introduced to the children and the procedures will be explained. The children will be submitted to an initial practice gait exam to become familiarized with the procedure (no data will be collected on this training run). The children will wear bathing suits to facilitate the placement of the markers. The skin will be cleaned with alcohol for better attachment of the markers on the exact sites. The markers will be enveloped in adhesive tape lined with microscopic glass spheres and attached to a plastic base with double-sided adhesive tape. The markers will be attached to the children in the orthostatic position, as suggested by Davis et al. (1991), [28] on the following anatomic structures:

Pelvis: Three markers will be positioned on the anterior superior iliac spines (right and left) and one between the posterior superior iliac spines.

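### The device-on evaluation, as worded, compares insoles with AFOs instead of insoles plus AFOs with AFOs alone, and the wear regimen does not settle which is meant

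*Protocol article*

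**What the plan says.** The protocol article describes the comparison in several places.

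- **Aim (Introduction).** The study is to determine what insoles and AFOs in combination do for functionality.
- **Arms (Abstract, Methods/Design).** The groups are "a control group using AFOs alone and an experimental group using both posture-control insoles and AFOs". Sample composition says the same in other words: AFOs exclusively, against AFOs combined with insoles.
- **Daily wear (Procedures).** For controls: "The control group will make daily and constant use of the AFOs". For the other arm: "The experimental group will make use of the posture-control insoles for six hours daily during the most active period of the day", after which the children "will remain using the AFOs the rest of the day".
- **Evaluation 1 (Procedures).** In this condition "the children will not use an assistance device". The examiner does not know the child's group.
- **Evaluation 2 (Procedures).** In this condition "the children will use either the posture-control insoles or the AFOs, depending on the group to which they belong". A different examiner performs it.

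**The concern.** The evaluation 2 sentence is the instruction that an examiner would follow on the day, and it does not match the stated contrast. The aim and both arm definitions call for the insole on top of the AFO, compared with the AFO alone. The instruction offers one device or the other, by group.

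If it is followed to the letter, the groups differ in two respects at once: the experimental child has gained an insole and lost an AFO. The Introduction itself credits the AFO with better alignment, less plantar flexion at initial contact and a steadier stance phase, so the plan does not regard its absence as neutral. A difference could appear although the insole adds nothing, or a real benefit of the combination could be hidden.

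Evaluation 2 is the only device-on condition described. If no child is measured in insole plus AFO, no later analysis can recover that state.

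**Working it through.** No stated figure turns on this point, so the check sets the contrasts side by side.

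**Notation.** At a given visit, let m_E(d) and m_C(d) be the mean outcomes of the experimental and control groups when tested in device state d. The states are 0 (no device), A (AFO), I (insole without AFO) and IA (insole with AFO). Any carry-over from daily wear is included in the group means.

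**Step 1: the contrast that the aim and arms call for, with devices on.**
Target = m_E(IA) − m_C(A)

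**Step 2: the contrast that evaluation 2 delivers if read literally.**
Literal = m_E(I) − m_C(A)

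**Step 3: the gap between them.**
Literal = Target − [m_E(IA) − m_E(I)]

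The bracket is the effect of having the AFO on, in a child who also wears the insole. It is zero only if the AFO does nothing in that state. It cannot be estimated, because m_E(IA) is never observed.

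**Step 4: does subtracting evaluation 1 help?**
[m_E(I) − m_E(0)] − [m_C(A) − m_C(0)]

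m_E(IA) is still absent, so a within-child change does not recover the target.

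**Step 5: evaluation 1 alone.**
m_E(0) − m_C(0)

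Both groups are in the same state. This is a randomised comparison of the two daily programmes, whatever those are, and the evaluation 2 wording does not touch it. It does not show how children function while wearing insole and AFO together.

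**Step 6: does the regimen sentence settle the matter?** Two readings of daily wear and two of the evaluation 2 sentence give four cases.

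| Daily wear in the experimental arm | Evaluation 2 sentence | What evaluation 2 measures |
|---|---|---|
| Concurrent (insole added to the AFO for six hours) | Literal: insole only | A state that these children do not wear in daily life; the AFO's absence is created by the test |
| Concurrent | Shorthand: insole plus AFO | The target contrast |
| Alternating (insole for six hours, AFO otherwise) | Literal: insole only | The state worn in the six active hours, against AFO; not what the insole adds to the AFO |
| Alternating | Shorthand: insole plus AFO | A combined state that the daily programme does not contain |

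Only the second case fits the aim, the arms and the daily wear together. The regimen sentence reads most naturally as alternating wear, since the AFO is assigned to the remainder of the day while controls wear theirs constantly. The Abstract's description of the follow-up visits, which counts them from use of AFOs or of insole and AFOs, leans towards concurrent wear. Nothing in the available text says that the two devices are worn together at evaluation 2. The flowchart might, but it is not shown in the text at hand.

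**The case against.** The strongest reply is that the sentence is shorthand. Procedures times the visits for all children by insole use, although controls receive no insoles, so the section already uses the word loosely. Naming each arm by its distinguishing device would be natural in such a text, and the Abstract and Sample composition both define the experimental arm as having both devices. This stands as a reason for moderate confidence. It does not remove the conflict, because an examiner could reasonably follow the sentence as printed.

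A second reply concerns alternating wear. If that is the intended programme, going without the AFO for six hours is part of the assigned treatment, and testing in insoles reflects how the children spend those hours. That also stands: under this reading the AFO's absence is not a bias. What remains is that the result is then insole against AFO and cannot be reported as the effect of the combination.

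A reader might also infer that the Berg Balance Scale breaks the no-device condition, because Instruments says: "The evaluation is performed with the child dressed and making use of his/her habitual orthosis and/or gait assistance device". The documents do not support this. The sentence is a general description of the scale. It mentions gait assistance devices, whereas the inclusion criteria admit only children who need none. The device conditions of this trial are set in Procedures.

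**Conclusion.** The evaluation 2 condition contradicts the stated aim and arm definitions, and the regimen sentence does not resolve the contradiction. Taken literally, the device-on comparison cannot show what the insole adds to the AFO. Confidence is moderate, because the wording may be loose and not intended.

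Three stronger conclusions are tempting but not supported:

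- **That the wrong contrast will certainly be run.** The text allows the shorthand reading, so this is a contradiction to correct and not proof of what examiners will do.
- **That the trial cannot answer any useful question.** Evaluation 1 remains a valid randomised comparison with an examiner unaware of group, and the article does not name evaluation 2 as the primary comparison.
- **That the damage can be stated as an inflated error rate or a loss of power.** The documents give no effect of removing an AFO. The 17 steps/minute under Sample description and characterization is the expected difference used for sizing. It draws on a study of cadence with and without a fixed AFO, but the article does not report it as the effect of an AFO. Moreover, if the tested states truly differ, a significant result is not a type I error. The fault would lie in attributing it to the combination.

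The size is therefore left as the bracket in step 3, with unknown sign and magnitude.

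**What to change.** Before enrolment, amend Procedures in one of two ways.

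1. **If concurrent wear is intended:** state that the insole is worn together with the AFO during the six hours, and set evaluation 2 to AFO plus insole in the experimental group and AFO alone in the control group.
2. **If alternating wear is intended:** restate the aim, arm definitions and conclusion as a programme of insoles for part of the day and AFOs for the rest, against constant AFO use. Rest the comparison of the two programmes on evaluation 1, and do not interpret evaluation 2 as the effect of the combination.

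Either change is a matter of wording. It needs no additional children or visits and leaves the stated sample size as it is. The timing matters, because a device state that was never tested cannot be reconstructed after follow-up.

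### The trial is called blind because one examiner is blind, but that examiner does only the device-off evaluation; no device-on assessment is covered by the claim

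*Protocol article*

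**What the plan says.** All of the blinding text is in the Procedures section of the protocol article. The evaluation process "will be performed under two different conditions". For the first: "Under the first condition (evaluation 1), the children will not use an assistance device". For the second, "the children will use either the posture-control insoles or the AFOs, depending on the group to which they belong". Staffing is then fixed: "Evaluation 1 and evaluation 2 will be performed by different examiners". The label follows: "Examiner 1 will not be aware of which group the children belong, thereby characterizing the investigation as a blind study". Nothing is said about whether the other examiner knows the group, and no rotation of examiners between conditions is described.

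The examiner-administered outcomes are listed in the same section: "The Berg Balance Scale, Timed Up-and-Go Test, Six-Minute Walk Test and modified Ashworth scale will be administered on the first day". On the Berg scale, the Instruments section adds: "The evaluation is performed with the child dressed and making use of his/her habitual orthosis and/or gait assistance device".

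The Statistical analysis section plans an intra-group analysis (repeated-measures ANOVA or Friedman) and an inter-group analysis (one-way ANOVA or Kruskal-Wallis). It does not say which evaluation condition enters either one.

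**The concern.** The article makes a claim about the whole investigation and gives one reason for it, and that reason covers only one of the two conditions. The device-on condition is where the device assigned by randomization is in use, so a reader would expect the blinding claim to matter most there. An assessor who can tell the arm while grading balance or tone may score the arms differently, and in a trial of 24 children a modest tilt is enough to matter.

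There is a second, conditional consequence. On the plain reading, one examiner always sees the child without a device and the other always sees the child with it. Examiner and device state then change together, so a device-on minus device-off difference in an examiner-administered outcome could not be attributed to the device alone.

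**Working it through.** The plan gives no figure for blinding, so there is none to reproduce. The check is a comparison of passages, followed by an illustration under assumed biases.

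**1. Who is blind, and to what (Procedures)**

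| | Evaluation 1 | Evaluation 2 |
|---|---|---|
| Device | none | depends on group |
| Examiner | Examiner 1 (by numbering) | a different examiner |
| Blinding stated | yes | not stated |

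The basis for the label reaches the first column only.

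**2. How many assessments are not covered**
- Both conditions at all five occasions (literal reading of Procedures): 5 + 5 = 10 assessments per child, of which 5 are device-on.
- First occasion device-off only (the Abstract lists it as without insoles or AFOs): 5 + 4 = 9, of which 4 are device-on.

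On either count, every device-on assessment falls outside the stated blinding.

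**3. Which comparisons are affected**

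Let μ be the device-off value, δ the device effect, e1 and e2 constant additive offsets of the two examiners, and g any extra scoring in favour of one arm (E) over the other (C) at Evaluation 2.
- Between arms, Evaluation 1: (μE + e1) − (μC + e1) = μE − μC. The offset cancels and the assessor is blind.
- Between arms, Evaluation 2: (μE + δE + e2 + g) − (μC + δC + e2) = (μE + δE) − (μC + δC) + g. The offset cancels; g does not.
- Within an arm, on minus off (without g): (μ + δ + e2) − (μ + e1) = δ + (e2 − e1). The device effect and the examiner difference cannot be separated.

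**4. Illustration**

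Inputs: 12 per arm (Sample description and characterization); two-sided 5% t-tests; no true effect. The biases, in SD units, and the within-child correlations ρ are assumptions.
- Between arms: noncentrality = g / √(2/12), 22 df, critical value 2.074. For g = 0.3: 0.3 / 0.408 = 0.735, giving 10.8%.
- On minus off within an arm: noncentrality = (e2 − e1) × √12 / √(2(1 − ρ)), 11 df, critical value 2.201. For 0.3 and ρ = 0.7: 0.3 × 3.464 / 0.775 = 1.34, giving 23.2%.

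| Assumed bias (SD) | Between arms, Evaluation 2 | On minus off, ρ = 0.5 | ρ = 0.7 | ρ = 0.9 |
|---|---|---|---|---|
| 0.1 | 5.6% | 6.2% | 6.9% | 10.9% |
| 0.2 | 7.6% | 9.7% | 13.0% | 29.3% |
| 0.3 | 10.8% | 15.8% | 23.2% | 56.3% |
| 0.5 | 21.6% | 35.3% | 53.2% | 94.0% |

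The first results column shows the effect of g. The last three show the effect of an examiner offset and apply only if such a contrast is tested.

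**5. Passages that do not fit together**
- Instruments has the Berg scale done with the habitual orthosis on; Evaluation 1 is device-free. If the Berg instruction were followed at Evaluation 1, Examiner 1 could see what the child wears, which might weaken the one blind that is stated.
- Procedures has Evaluation 2 with insoles or AFOs according to group; the Abstract and Sample composition describe the experimental group as using both. How easily Evaluation 2 reveals the group depends on which applies.

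**The case against.** **Examiner 2 is nowhere said to be unblinded.** Correct. The documents are silent, and knowledge of group is an inference from a device that depends on group. If both arms wear AFOs and differ only by an insole, the visible difference would be smaller. This limits the wording to not stated to be blind. It does not rescue a study-wide label that rests on the other examiner.

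**Separate examiners protect the blind.** Also correct. If one person did both evaluations, that person would see the device. The split is a sensible trade-off and should stay; its price is that on-versus-off contrasts carry the examiner difference.

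**The plan specifies no on-minus-off test.** This stands. The intra-group analysis may mean change over the five occasions within one condition. A reader might infer that examiner is confounded with the randomized comparison; step 3 shows that a constant offset cancels there. The Abstract's list, which starts without any accessory and continues with device use, makes an off-to-on comparison possible but does not fix one.

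**Much of the outcome set is instrumented.** The sample size rests on gait cadence, measured by cameras and force plates. The Timed Up-and-Go is in seconds and the six-minute walk in metres. These are less exposed than Berg and Ashworth, though not immune: marker placement for the gait analysis is manual ("The skin will be cleaned with alcohol for better attachment of the markers on the exact sites").

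**Children and parents know the device.** True, but this contradicts nothing, since the article claims blinding only for Examiner 1.

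**Conclusion.** The point holds in a limited form. The article labels the whole investigation blind, but its stated basis covers Evaluation 1 only, so the label is unsupported for every device-on assessment (4 of 9 or 5 of 10 per child, depending on how the first occasion is read). The exposure is greatest for Berg and modified Ashworth. Under assumed scoring biases of 0.1 to 0.5 SD, the between-arm false-positive rate at Evaluation 2 would be 5.6% to 21.6%. These rates are illustrative: no bias is given in the documents, and the t-test is only an approximation for graded scales.

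A reader might infer that half of all assessments are definitely unblinded, or that device and examiner effects are inseparable throughout the trial. The documents support neither. Examiner 2's knowledge of group is a strong inference, the half depends on a device-on assessment before device use, and a constant examiner difference leaves between-arm comparisons intact. The confounding concerns on-versus-off contrasts in examiner-administered outcomes, if made, and assumes one fixed examiner per condition.

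This is not a matter of detail left to a fuller document: the article itself states the claim, its reason and the examiner split.

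**What to change.** - Replace the label with: *assessor-blind for Evaluation 1 only; Evaluation 2 is open*.
- At each visit do Evaluation 1 first, with the devices out of Examiner 1's sight.
- Process gait and force-plate files under codes that do not show the group.
- For examiner-scored outcomes, report the between-arm results of Evaluation 1 as the blinded evidence and those of Evaluation 2 as open assessment. Device-on results stay in the report, which the aim of studying the combination's effect on functionality needs.
- Do not interpret on-minus-off differences in examiner-administered outcomes as device effects.
- Reconcile the Berg instruction in Instruments with the device-free Evaluation 1, and the insoles-or-AFOs wording in Procedures with the combined use described in the Abstract and Sample composition. Which version applies is for the investigators to state.

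The cost is wording, test order and file coding, with no extra children or examiners. The downside is a narrower blinding claim, an open-assessment caveat on device-on results, and blinded evidence for examiner-scored outcomes that concerns function without the device.

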### Flowchart

The project will be carried out in accordance with the following flowchart (Figure 3).

